## Human Participants Research Checklist

***Complete the following if your study involved human participants or human participants' data. These questions should be addressed for prospective and retrospective studies.***

1. Did you obtain ethics approval for this study?

- If yes, please upload (file type "Other") the original approval document you received from your ethics committee. If the original document is in another language, please also provide an English translation.

☒ Uploaded ☐ N/A

⇒ **Yes, the study was ethically approved, and the approval letter is uploaded in the recommended file type (other)**

- If you did not obtain ethical approval, please explain why this was not required below.

2. If you prospectively recruited human participants for the study – for example, you conducted a clinical trial, distributed questionnaires, or obtained tissues, data or samples for the purposes of this study, please report in the Methods:

- i. the day, month and year of the **start and end** of the recruitment period for this study.
- ii. whether participants provided informed consent, and if so, what type was obtained (for instance, written or verbal, and if verbal, how it was documented and witnessed). If your study included minors, state whether you obtained consent from parents or guardians. If the need for consent was waived by the ethics committee, please include this information.

☐ Completed ☒ N/A

**This study is a protocol. Patients have not yet been enrolled.**

3. If you are reporting a retrospective study of medical records or archived samples, please report in the Methods section:

- i. the day, month and year when the data were accessed for research purposes
- ii. whether authors had access to information that could identify individual participants during or after data collection

☐ Completed ☒ N/A

[figure not shown]

| Titre du projet: Effectiveness of music therapy on the efficacy of noninvasive ventilation in acute exacerbation of chronic obstructive pulmonary disease: a randomized controlled clinical trial protocol |                                                                                                                                                                                                                                                                                                     |
| Type of study                                                                                                                                                                                              | Retrospective study:  Prospective study: 
Observation study:  Intervention study: 
Autres (Préciser) :A randomized controlled clinical trial protocol                              |
| Scope of the study                                                                                                                                                                                         | National research programme  International 
Thesis of medicine  Master/CEC of medicine  Theses of science 
Other (Please specify):..... research article ..... |
| Principal Investigator: project leader                                                                                                                                                                     | Researcher:                                                                                                                                                                                                                                                                                  |

| Chronic obstructive pulmonary disease (COPD) is a major global health concern, ranking as the third leading cause of death worldwide [1]. Non-invasive ventilation (NIV) is a cornerstone therapeutic strategy for managing patients with severe exacerbations, particularly those with hypercapnic encephalopathy [3]. However, the efficacy of this |

technique is dependent on several factors. In fact, patient anxiety and discomfort, despite appropriate pressure settings and equipment, can lead to premature mask removal and excessive air leaks [4]. In recent years, there has been growing interest in applying music therapy in medical contexts, particularly in intensive care units. Recent studies have explored the potential benefits of music therapy in patients with acute respiratory failure requiring invasive mechanical ventilation [6–8]. Some studies have demonstrated positive effects of music therapy on anxiety, pain, analgesic use, delirium, and overall patient satisfaction [6,7,9,10]. Music therapy can also reduce agitation in confused patients, improve mood, and facilitate communication [6]. Within the context of NIV, music therapy may serve as a valuable non-pharmacological intervention. By enhancing patient acceptance and tolerance of the technique, music therapy can potentially improve the efficiency of NIV sessions [11]. There is limited literature on the impact of music therapy on NIV experience. To the best of our knowledge, no studies have yet examined the intra-session effects of music therapy on critically ill COPD patients undergoing NIV for acute exacerbation. By addressing the psychological and emotional challenges associated with NIV, music therapy could potentially improve patient acceptance, adherence to this technique and then clinical outcomes.

Objective(s) of the work:

to assess the impact of music therapy on the efficacy of NIV in patients with Acute Exacerbation of Chronic Obstructive Pulmonary Disease (AECOPD). We hypothesize that intra-session music therapy can improve NIV efficacy and tolerance in AECOPD compared to conventional care.

#### **Methodology (briefly)**

##### **1-Study type:**

Mono-center, prospective, randomized, single-blinded, parallel-group trial

Location of study: Intensive Care Unit (ICU) of Farhat Hached Hospital in Sousse, Tunisia

Period: From February 2025 to August 2025

##### **2-Population under study:**

##### **Target population:**

- **Inclusion criteria:** Consecutive adult patients (≥18 years) with COPD admitted to the ICU for an AECOPD

will be included. Eligibility requires meeting the GOLD criteria for COPD, having a pH <7.35, and being assessed as suitable for NIV by the attending physician.

- **Exclusion Criteria:**

- Patients unable to tolerate NIV or for whom NIV is contraindicated
- Patients with severe hearing impairment or deafness
- Patients for whom life-sustaining therapies have been withdrawn
- Patients who have received antidepressant or antipsychotic medications in the previous two months
- Aversion of music as assessed by personal interview

#### **Sampling procedure**

Randomization: All inclusion and exclusion criteria will be thoroughly reviewed. Eligible participants will then be randomly allocated in a 1:1 ratio to either the intervention group (music) or the control group using a computer-generated random sequence to ensure allocation concealment and minimize selection bias.

Blinding of the participants is not possible due to the nature of the intervention; however, primary outcome assessors and data analysts will be blinded to group allocation to reduce assessment and analysis bias according to the prospective randomized open blinded endpoint (PROBE) method.

#### **Sample size:**

the final sample size is set at 38 patients per group in either a 'musical intervention' group or a 'control' group,

Recruitment is planned over a 6-month period, with a target enrolment of 76 participants.

#### **3-Data collection:**

Measurement instrument/data collection sheet

##### **Day 1: baseline assessment (t0)**

Before randomization, demographic and baseline measurements will be collected for each patient, including sociodemographic data (such as age and sex), the COPD Assessment Test (CAT), and modified Medical Research Council (mMRC) scores, along with baseline characteristics including the Charlson Comorbidity Index (CCI) and Simplified Acute Physiology Score II (SAPS II).

After the baseline assessment, participants will be randomised into one of the two groups.

#### **During NIV session**

Primary and secondary outcomes will be collected by the principal investigator, who will conduct all assessments while remaining blind to the participants' group allocations, data collection, and analysis.

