#### **Secondary Endpoints**

- Unplanned interventions: The number of unplanned interventions required by caregivers during the NIV session will be documented.
- Changes in respiratory and cardiovascular parameters: These parameters will be assessed before the NIV session, immediately after proper setup (5 minutes), and then at hourly intervals (h1, h2, h3, h4):
  - Respiratory rate (RR)
  - Peripheral oxygen saturation (SpO2)
  - Tidal volume (Vt)
  - Leak rate
  - Heart rate (HR)
  - Systolic blood pressure (SBP)
  - Diastolic blood pressure (DBP)
- Respiratory comfort: assessed using a digital visual scale, changes in respiratory comfort will be measured (h0, h2, h4).
- Neurological assessment (h0, h2, h4):
  - Encephalopathy score (Kelly-Matthay scale)
  - Glasgow Coma Scale

- Richmond Agitation-Sedation Scale (RASS)
- Patient-reported outcomes (h0, h2, h4):
  - Borg Dyspnea Scale (BDS)
  - Verbal Numeric Rating Scale (VNS) for pain assessment
- Psychological assessment (h0, h4):
  - Rapid Clinical Test For delirium (4 AT)
  - State Trait Anxiety Inventory (STAI)
  - Spielberger's trait anxiety inventory
  - Perceived stress scale (PSS)

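### The protocol says one investigator makes every in-session assessment blind to allocation; as described this is not credible, and the claim should be limited to PCO2 and the data analyst

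*Protocol*

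**What the plan says.** Three sections of the protocol describe blinding, each with a different scope.

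- **Study type** gives the design label only: "Mono-center, prospective, randomized, single-blinded, parallel-group trial". It does not say who is blinded.
- **Sampling procedure** concedes "Blinding of the participants is not possible due to the nature of the intervention" and then says that "primary outcome assessors and data analysts will be blinded to group allocation", naming the PROBE approach. Assessors of secondary outcomes are not mentioned.
- **During NIV session** goes further: "Primary and secondary outcomes will be collected by the principal investigator, who will conduct all assessments while remaining blind" to group allocation. The same sentence lists data collection and analysis among the things this person is blind to.

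The objective places the intervention inside the session: "We hypothesize that intra-session music therapy can improve NIV efficacy and tolerance in AECOPD compared to conventional care". Under Secondary Endpoints, respiratory and cardiovascular parameters are taken before NIV, 5 minutes after set-up and at h1, h2, h3 and h4. Comfort, the neurological scales, dyspnoea and pain are scored at h0, h2 and h4, and the psychological instruments at h0 and h4.

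**The concern.** One person is to be present through a session in which one arm hears music and the other does not, and is nevertheless said not to know the arm. The protocol gives no reason to expect this: it mentions no matching equipment in controls, no music-free assessment window and no separate assessor. A person who collects data also cannot be blind to data collection.

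What is at stake is how the secondary results are read. The hypothesis has two halves, efficacy and tolerance. Efficacy rests on PCO2. Tolerance rests largely on comfort, agitation, anxiety and unplanned interventions. If During NIV session stands, the observer-rated scales could be reported as blinded assessments when the plan provides nothing to make them so, and readers would give them more weight than they can bear.

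**Working it through.** The protocol gives no figure for this point, so the check is to classify the outcomes and ask what a blind collector would protect.

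**Step 1. Count the secondary outcomes** (Secondary Endpoints): unplanned interventions 1, respiratory and cardiovascular parameters 7, comfort 1, neurological 3, patient-reported 2, psychological 4. Total: 1 + 7 + 1 + 3 + 2 + 4 = 18.

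**Step 2. Sort them by who determines the value.**

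| Source of the value | Outcomes | Number | Would a blind collector protect it? |
|---|---|---|---|
| Observer rating | Kelly-Matthay, Glasgow Coma Scale, RASS, 4AT | 4 | Yes, if the blinding were real |
| Patient rating | Comfort, Borg, pain, STAI, trait anxiety, PSS | 6 | No: the rater is the unblinded patient |
| Caregiver action | Unplanned interventions | 1 | No: no caregiver blinding is described |
| Physiological or ventilator parameter | RR, SpO2, Vt, leak, HR, SBP, DBP | 7 | Less exposed, though the protocol does not say how each is read |

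Check: 4 + 6 + 1 + 7 = 18.

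**Step 3. Compare the two blinding statements.** Sampling procedure covers the primary outcome and the analysis. During NIV session covers the primary and all 18 secondary outcomes. The difference between the two is the secondary outcomes, and among these the four observer-rated scales are where assessor blinding matters most.

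**Step 4. Ask whether the wider claim can hold.** Since the principal investigator makes all assessments, that person is at the bedside at 5 minutes, h1, h2, h3 and h4. The first scoring of the neurological scales after the start of NIV is at h2, by which time there have been two attendances (5 minutes and h1) in a session with or without music. With no masking described, allocation can be presumed known by then.

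**Step 5. Primary outcome.** PCO2 is a measured blood value at h2 and h4. Knowing the arm gives little room to alter the reading, so the claim in Sampling procedure can hold for it.

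**Illustration only.** The protocol gives no size for any rating bias, so the shifts below are assumptions. With n = 38 per arm (Sample size), a two-sided 5% test and no true effect, a spurious difference of b SD in a continuous score gives, by normal approximation,

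P(p < 0.05) = 1 − Φ(1.96 − b/√(2/38)) + Φ(−1.96 − b/√(2/38)), where √(2/38) = 0.229.

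| Assumed b (SD) | 0 | 0.1 | 0.2 | 0.3 |
|---|---|---|---|---|
| Chance of p < 0.05 | 5.0% | 7.2% | 14.1% | 25.8% |

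This shows how sensitive a trial of 76 patients would be if such a bias existed. It is not evidence that one does. It does not apply to unplanned interventions, which are to be compared by chi-square or Fisher's exact test, and it is only approximate where Mann-Whitney is used.

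**The case against.** The best defence has four parts.

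1. **Blinding has not been shown to be impossible.** A reader might infer that it is. The protocol does not say whether the music comes through headphones or a loudspeaker, how long it lasts, or whether it plays at assessment times, and the methodology is headed as a brief account. This stands. The supportable statement is that the claim is not credible as described.
2. **The primary endpoint is largely untouched.** This also stands. A reader might conclude that the blinded-endpoint design fails as a whole. The text does not support that, because blinded reading of PCO2 and blinded analysis remain feasible.
3. **The protocol already discloses that patients are not blinded.** True, so the open status of the six self-rated scales can be worked out from the text. It would be wrong to say that the sentence under During NIV session compromises eleven outcomes. It bears directly on four. The other seven are unprotected for reasons of their own, one of which the protocol states openly.
4. **The sentence may be badly constructed.** It may mean that the investigator stays blind throughout data collection and analysis. That reading removes the self-contradiction but keeps the claim of blind bedside assessment, and that claim is the substance of the point.

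**Conclusion.** The point holds in a limited form. The protocol claims assessor blinding for all outcomes without describing anything that could provide it, and the claim goes beyond its own randomisation section. The direct effect is on four of 18 secondary outcomes. Seven more, six patient-rated and one caregiver-driven, would be open-label even with a truly blind collector, and the protocol should say so plainly. The primary outcome is little affected.

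This rests on two readings of the text: that music plays during the session in one arm only, and that the principal investigator is personally present at each scheduled assessment, as the words about conducting all assessments imply. An unstated masking procedure could change the conclusion for the four observer-rated scales, but not for the other seven.

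The false-positive rates under Working depend wholly on assumed shifts and should not be quoted as an estimate of bias in this trial.

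**What to change.** Reconcile the three sections so that they make one claim.

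- **Study type:** say who is blinded, or refer to Sampling procedure, instead of leaving the single-blind label unexplained.
- **Sampling procedure:** limit the claim to PCO2, read from results labelled only with study number and time, and to the data analyst.
- **During NIV session:** remove the statement that the investigator conducts all assessments blind, and delete the reference to being blind to data collection.
- **Secondary Endpoints:** state that the observer-rated, patient-reported and caregiver-driven outcomes are open-label and will be interpreted as supportive.

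If the sponsor already has a procedure that masks the bedside assessor, describing it could support keeping the claim for the four observer-rated scales. It would have to cover every attendance. Silencing the music only at h2 and h4 would not be enough, because the same investigator is present at 5 minutes, h1 and h3.

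The change is to wording and to the labelling of blood-gas results. It adds no patients and no assessors, and the protocol states that enrolment has not begun. The price is a less favourable description of the trial's blinding and more cautious language about tolerance.

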#### **Primary Endpoint**

The primary outcome of the study will be the efficacy of NIV measured by the reduction in arterial Pressure of Carbon dioxide (PCO2). This will be calculated as the difference between baseline PCO2 and the PCO2 levels recorded at specific time points during the NIV session (h2, h4):  $\Delta PCO_2 = \text{Baseline } PCO_2 (t_0) - \text{Endpoint } PCO_2 (t_1, t_2)$ .

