#### Statistical analysis and expected results

The statistical analysis will be conducted using SPSS version 20. All continuous variables will be expressed as mean  $\pm$  SD or median with interquartile range (IQR) (25th-75th percentile), depending on the normality of distribution assessed by the Shapiro-Wilk test. Categorical variables will be summarized as frequencies and percentages.

For the primary endpoint, the mean reduction in PCO2 between the intervention (music therapy) and control groups ( $\Delta$ PCO2= baseline PCO2 – endpoint PCO2) will be compared using a student t-test or Mann-Whitney U test, as appropriate. Repeated measures analysis of variance (ANOVA) or a mixed-effects model approach will be used to analyze within-group changes across time points (h1, h2, h3, h4) ensuring adjustments for potential correlations within repeated measures.

For secondary outcomes:

- Respiratory and cardiovascular parameters: Differences between groups over time will be analysed using repeated measures ANOVA or mixed-effects models.
- Respiratory comfort and patient-reported outcomes (e.g., BDS, VNS): group comparisons will be performed using t-tests or Mann-Whitney U tests for continuous variables, with effect sizes and 95% confidence intervals reported.
- Neurological and psychological assessments: changes from baseline (h0) to endpoint (h4) will be analysed

using paired t-tests or Wilcoxon signed-rank tests within groups, and independent t-tests or Mann-Whitney U tests between groups.

- For categorical secondary outcomes (e.g., unscheduled interventions): comparisons between groups will be made using a chi-square test or Fisher's exact test where appropriate.

Missing data will be handled using multiple imputation techniques if the proportion of missing data is significant, ensuring unbiased estimates. Sensitivity analyses will be performed to assess the robustness of the results, particularly for the primary outcome.

All statistical analyses will be conducted on an intention-to-treat basis at a bilateral 5% alpha risk. Results will be interpreted with both statistical significance ( $p < 0.05$ ) and clinical relevance considered. Analyses will be performed by an independent investigator blinded to treatment allocation, ensuring unbiased interpretation of the data.

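### The primary PCO2 reduction is defined at both h2 and h4 but tested as one quantity, with no deciding time point or decision rule, so the 5% error rate is not guaranteed

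*Protocol*

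**What the plan says.** The Primary Endpoint section of the protocol takes NIV efficacy as the primary outcome, "measured by the reduction in arterial Pressure of Carbon dioxide". The reduction is baseline PCO2 minus the "levels recorded at specific time points during the NIV session (h2, h4"). The formula beside it carries two endpoint times, t1 and t2, under one symbol.

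The section on statistical analysis and expected results compares the mean reduction between groups. It says this reduction "will be compared using a student t-test or Mann-Whitney U test, as appropriate". Endpoint PCO2 is in the singular there and is not tied to a time. The same paragraph adds a repeated-measures ANOVA or mixed model, which "will be used to analyze within-group changes across time points (h1, h2, h3, h4").

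On error control, the section says: "All statistical analyses will be conducted on an intention-to-treat basis at a bilateral 5% alpha risk". The threshold for significance is p < 0.05. The protocol gives no order of testing, no split of alpha between the two times, and no requirement that both be significant.

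**The concern.** A t-test or a Mann-Whitney test takes one value per patient, and the primary endpoint supplies two. The protocol leaves open which of them decides the trial.

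Two things are at stake. First, the main conclusion may be undefined: with a significant difference at h2 but not at h4, or the reverse, nothing in the protocol says whether the trial has met its objective. Second, the open choice could be settled after the results are known, or either result could be presented as the primary one. The real false-positive rate would then exceed the stated 5%.

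Which measurement decides the trial is part of the endpoint definition. The protocol sets out that definition itself, so this is not merely a detail left for an analysis plan.

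**Working it through.** **Inputs.**
- Two primary time points, h2 and h4 (Primary Endpoint).
- Two-sided alpha of 0.05 (statistical analysis section).
- 38 patients per group (Sample size).
- Correlation rho between the reductions at h2 and h4: not given, so it is an assumption, shown from 0 to 0.95.

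**Does another sentence settle it?** The repeated-measures model in the primary paragraph does not. It addresses change within each group, so it gives no between-group contrast. Its times include h1 and h3, whereas the primary PCO2 measurements are defined only at t0, h2 and h4. Between-group differences over time are assigned to a model only for the respiratory and cardiovascular secondary outcomes.

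**Readings under which the stated 5% holds.** One test at one pre-named time, or one test of a pre-named summary of both times, has alpha 0.05. If both times must be significant, alpha is at most 0.05. Simulated t-tests with no true effect at either time gave 0.88%, 1.55% and 3.01% for rho 0.5, 0.7 and 0.9.

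**Reading under which it fails.** If significance at either time counts, the false-positive rate is 1 − P(|Z1| < 1.96 and |Z2| < 1.96), where Z1 and Z2 are standard normal with correlation rho. With rho = 0 this is 1 − 0.95² = 0.0975. The simulation used two t-tests with 38 per arm and 100,000 runs per value of rho.

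| rho | Formula | Simulation |
|---|---|---|
| 0 | 9.75% | 9.77% |
| 0.5 | 9.07% | 9.08% |
| 0.7 | 8.35% | 8.28% |
| 0.8 | 7.81% | 7.80% |
| 0.9 | 7.04% | 7.08% |
| 0.95 | 6.46% | not run |

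The rate returns to 5% only at rho = 1.

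**Which rho is plausible?** Both reductions subtract the same baseline value. If the three PCO2 measurements have equal variance s² and equal pairwise correlation r, the covariance of the two reductions is s²(1 − r − r + r) = s²(1 − r), and each has variance 2s²(1 − r). Their correlation is then 0.5 whatever r is. Zero is therefore only an outer bound, and 0.5 to 0.9 is a reasonable working range.

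**Price of keeping both times primary.** The Sample size section gives no effect size, SD or power, so the calculation is in SD units with power assumed. At two-sided 5% and 80% power, 38 per group detects (1.960 + 0.842) × √(2/38) = 0.64 SD. For that difference, with 0.025 per time point:
- Power per time point is Φ(2.802 − 2.241) = 71%.
- Restoring 80% needs 38 × (3.083/2.802)² = 46.0, and 47 per group after rounding up the unrounded value.

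If 90% power is assumed, the detectable difference is 0.74 SD, power per time point falls to 84%, and 45 per group are needed.

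**The case against.** A reader might infer that the plan tests h2 and h4 each at 5% and lets either one win, so that the stated alpha is simply wrong. The document does not say that. The analysis section speaks of one mean reduction and one test, and no sentence prescribes two tests or an either-wins rule. The text is equally open to one test at an unnamed time, a summary of both, or a requirement that both succeed, and none of those inflates alpha. This objection stands: the inflation is what the wording permits, not what it lays down.

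Three other defences are weaker. The methodology is headed as brief, and an analysis plan may exist that settles the matter. That argues for caution about the size of the problem, but it does not reconcile a two-time endpoint with a one-value test within the protocol. Blinding the analyst to allocation does not prevent the time point being chosen once results are available. The analysis section does use h4 as the endpoint, where "changes from baseline (h0) to endpoint (h4) will be analysed", but this covers only the neurological and psychological assessments. The Primary Endpoint section attaches the word to both times.

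A reader might also extend the point to the long list of secondary outcomes judged at the same threshold. That is a separate matter, commonly left to an analysis plan, and nothing here depends on it.

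**Conclusion.** The concern holds as a gap in the endpoint definition: two primary times, one test, and no rule connecting them. The 5% level is not guaranteed, and discordant results at h2 and h4 would leave the trial without a defined outcome. That second consequence needs no assumption about correlation.

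The false-positive rate of about 7% to 9% rests on two assumptions: that either time counts as success or the time is picked after seeing data, and that rho lies between 0.9 and 0.5. The figure of 9.75% is an upper bound under independence, which the shared baseline makes implausible. It would overstate the case to say that the trial's alpha is already wrong. Because the gap affects the trial's main conclusion, it should be closed before the first patient is enrolled.

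**What to change.** Name one time point, in both the Primary Endpoint and the statistical analysis sections, as the only primary contrast. For example: *The primary endpoint is the between-group difference in mean PCO2 reduction from t0 to h4, tested two-sided at 5%. The reduction at h2 is a secondary endpoint, tested at the same level only if the h4 difference is significant.*

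The h4 time is a natural choice, as the last scheduled assessment of the session and the endpoint already used for the neurological and psychological outcomes. The investigators may justify h2 instead. What matters is that the choice is fixed in advance.

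The cost is about two sentences. Testing in this order keeps alpha at 5% with 38 per group and needs no extra data or patients. The protocol's checklist states that no patient has yet been enrolled, so the change can be made cleanly.

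If both times are to stay primary, the plan should state the rule and acknowledge its price. An equal alpha split lowers power per time point as calculated above. Holm is never less powerful than that split, but its first step is also at 0.025, so it is not free at 38 per group. Requiring significance at both times needs no alpha split, but it is a harder target and should be stated as such.
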